### 2.11. Sample size estimation

Assuming a rate of good neurological function in both the study and control groups (180 d) of not less than 51%, a noninferiority threshold Δ=–10%, a sample ratio of the study and control groups of 1:1, a unilateral test level (α = 0.025), a total certainty of 80%, and a 5% loss rate, the total sample size required is 202 patients and 101 patients in each group.

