### 2.12. Statistical analysis methods

All data will be analyzed according to the intentionality analysis and will follow the protocol analysis statistics. Statistical descriptions will be used to compare the baseline information. The mean ± standard deviation or median (interquartile range) will be used to express the measurement data, and rates or percentages will be used for count data. For measurement data, a *t* test or Mann–Whitney *U* test will be used to detect differences between the groups. The Chi-squared test will be used to analyze the count data.

All data will be analyzed using SPSS 23.0 (IBM Corporation, Armonk, NY) software, and *P* < .05 (2-sided) will be considered a statistically significant difference.

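### The trial is sized for noninferiority, but the stated analysis tests only for a difference and never uses the margin

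*Protocol article*

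**What the plan says.** Section 2.11 (Sample size estimation) gives the framework. It uses "a noninferiority threshold Δ=–10" percent, "a unilateral test level (α = 0.025") and "a total certainty of 80" percent. It assumes a "rate of good neurological function in both the study and control groups (180 d) of not less than 51" percent, with 1:1 allocation and 5% loss, and arrives at 101 per arm, 202 in total.

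Section 2.12 (Statistical analysis methods) gives the analysis. Measurement data go to a t test or Mann-Whitney U test for differences between groups. For the rest, "The Chi-squared test will be used to analyze the count data". The only decision rule is P < .05 ("2-sided) will be considered a statistically significant difference"). The section has no confidence interval, no margin-based test and no noninferiority criterion. The margin appears nowhere in the article outside section 2.11.

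Section 2.8 gives the primary outcome as neurological functional status at 90 days, assessed by mRS and NIHSS scores. It sets no cut-off for good function. Section 2.11 refers to good function at 180 days.

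**The concern.** The two sections address different null hypotheses. Section 2.11 implies H0: study rate minus control rate ≤ -10 points. The tests in section 2.12 address H0: difference = 0. A rate of good neurological function is count data, so under section 2.12 it goes to the chi-squared test.

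A non-significant chi-squared result does not show that ECASES is at most 10 points worse. It may only mean that the trial is small. A significant result against ECASES does not say whether the deficit exceeds the margin. If the arms turn out similar, which is what the sizing assumes, the written plan gives no rule for a noninferiority conclusion. Any such conclusion drawn from P > .05 would have no error control.

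**Working it through.** **Inputs**
- From section 2.11: 51% in both arms, margin 10 points, one-sided alpha 0.025 (z = 1.960), power 80% (z = 0.842), 5% loss, 101 per arm.
- Evaluable per arm: 101 × 0.95 = 95.95, taken as 96.
- Assumed here, not in the article: true rates of 41% v 51% (exactly at the margin) and 61% v 51%.

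**1. The plan's own figure.** n per arm = (1.960 + 0.842)² × [p₁(1-p₁) + p₂(1-p₂)] / (p₁ - p₂ + margin)².
- Stated inputs, 51% v 51%: 7.849 × 0.4998 / 0.01 = 392.3, so 393 per arm. With 5% loss, 393 / 0.95 gives 414 per arm, 828 in total. The stated 202 is not reproduced.
- Study 61%, control 51%: 7.849 × 0.4878 / 0.04 = 95.7, so 96 per arm, and 96 × 1.05 gives 101. This matches, but 61% is not stated anywhere.

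**2. The chi-squared test when ECASES is truly 10 points worse (41% v 51%, 96 per arm).**
- SE under H0: √(2 × 0.46 × 0.54 / 96) = 0.0719. SE under the true rates: √((0.41 × 0.59 + 0.51 × 0.49) / 96) = 0.0716.
- Power = Φ((0.10 - 1.960 × 0.0719) / 0.0716) = Φ(-0.57) = 0.283, so about 72% of trials are non-significant.
- Exact binomial enumeration gives 71.4% non-significant.
- By the same enumeration, a rule requiring the lower limit of a Wald 95% interval to exceed -10 points passes 2.9% of the time, close to the intended 2.5%.

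**3. The chi-squared test when the arms are equal (51% v 51%).** Exact enumeration gives 94.9% non-significant, and 2.6% significant in favour of ECASES. Only that 2.6% would let the stated test imply noninferiority.

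**4. What a margin-based analysis can deliver at this size (51% v 51%, 96 per arm).**
- SE = √(2 × 0.51 × 0.49 / 96) = 0.0722. Half-width of the 95% interval = 1.960 × 0.0722 = 14.1 points, wider than the margin. ECASES would have to be observed about 14.1 - 10 = 4.1 points better to pass.
- Noninferiority power = Φ(0.10 / 0.0722 - 1.960) = Φ(-0.57) = 28%. Exact enumeration with the Wald interval gives 31%.

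**5. The same under the unstated 61% v 51%.** Noninferiority power = Φ(0.20 / 0.0713 - 1.960) = Φ(0.85) = 80% (exact 81%). The chi-squared test is significant for ECASES 28.5% of the time. In about 53% of such trials the interval clears the margin while the planned test reports only a non-significant result.

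**The case against.** **A reader might infer that no stated analysis can ever answer the noninferiority question.** That goes too far. A significant chi-squared result favouring ECASES puts the difference above 0, and therefore above -10 points. The route exists, but it is open only about 2.6% of the time when the arms are equal.

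**A reader might infer that the alpha levels conflict.** They do not. One-sided 0.025 corresponds to the lower limit of a two-sided 95% interval. What is missing is the comparison with the margin.

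**A reader might infer that switching tests drops power from the planned 80% to about 29%.** The stated inputs do not support this. The 29% and the 80% both belong to 61% v 51%, a study rate the article never gives. At the stated 51% in both arms, a correct noninferiority analysis has only about 28-31% power.

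**Section 2.11 may be the faulty section.** Noninferiority appears only there. The stated aim is to evaluate efficacy and safety, and the design section says only that the groups will be compared. This stands: the documents do not show which framework was intended.

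**A statistical analysis plan may hold the noninferiority test.** The choice of interval method and similar detail can be left to such a plan. But section 2.12 is not silent: it fixes the tests and the decision rule for all data. A later noninferiority criterion would change that rule, not fill a gap in it. Nor does any text say that P > .05 will be read as noninferiority. That is a risk the wording leaves open, not something the authors state.

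**Conclusion.** The point holds. The design and analysis sections state incompatible hypotheses, and the difference in section 2.12 governs the trial's main conclusion, so it must be fixed. Apart from a significant result in favour of ECASES, the stated analysis cannot establish noninferiority. With a deficit exactly at the margin, chi-squared would be non-significant about 71% of the time, against about 3% wrongful passes for a margin-based interval.

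These figures assume 96 evaluable patients per arm, a control rate of 51%, and a binary good-outcome endpoint that the article does not define. The mismatch itself does not depend on them: the hypotheses differ at any sample size. That 202 does not follow from the stated inputs is a separate fault, but it limits what the correction can achieve.

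**What to change.** Reconcile sections 2.11 and 2.12 before any outcome data are compared.

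**If noninferiority is the aim:**
- Name one binary good-outcome endpoint with its definition, and one time point. Section 2.8 says 90 days and section 2.11 says 180 days.
- State H0: study minus control ≤ -10 points.
- Make the primary analysis the risk difference (ECASES minus control) with a two-sided 95% confidence interval, by a named method such as Newcombe or Miettinen-Nurminen.
- Declare noninferiority only if the lower limit exceeds -10 points. Report it for both the intention-to-treat and per-protocol sets, which section 2.12 appears to intend already.
- Test superiority (lower limit above 0) only after noninferiority is met. Keep the difference tests for secondary outcomes.

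**If superiority is the aim:** rewrite section 2.11 with a superiority hypothesis, a justified effect and a matching sample size, and remove the margin.

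**Cost.** The analysis wording takes about a paragraph and no new data. It does not rescue the power. With 51% in both arms and 96 per arm, the trial would fail to show noninferiority about 69-72% of the time. The power statement must therefore be restated: either declare and justify the 61% v 51% assumption that gives 80%, or recalculate the number of patients (about 828 from the stated inputs).

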### 2.13. Technology line

The clinical intervention technology roadmap is shown in Fig. 1.

**Figure 1. F1:**
[figure not shown]
Clinical intervention technology roadmap.

## 3. Discussion

Acute carotid stenting procedures associated with arterial thrombectomy have been performed by many neurointerventionists. The TITAN study, a retrospective pooled analysis of data from acute ischemic stroke patients with tandem lesions in the anterior circulation from 18 international comprehensive stroke centers (including more than 450 patients), showed that acute stenting of an extracranial internal carotid artery lesion was associated with improved reperfusion (mTICI 2b-3 and mTICI 3)^[12,13]^ without an excess risk of intracranial hemorrhage or mortality,^[14]^ as previously reported in 2 meta-analyses of case series.^[15,16]^ However, prospective controlled data are lacking regarding the efficacy and safety of carotid stenting in the acute phase of stroke reperfusion, particularly in the context of antiplatelet therapy.

According to research studies and work experience, intracranial hemorrhage is related to the preoperative infarct size, infarct site (basal ganglia area), contrast medium extravasation, or bleeding detected by intraoperative DynaCT after vascular recanalization in acute stroke with large-vessel occlusion.^[17,18]^ Postoperative recovery of neurological function (improvement of cerebral ischemia) is related to postoperative vascular patency and collateral circulation compensation.^[19]^ Accordingly, the ECASES system proposes a bleeding risk score and an ischemic risk score based on the above factors and then suggests an individualized stenting decision by weighing bleeding and ischemic risks with a sufficient theoretical basis. This study uses a randomized, double-blind design in which, for each subject, 2 types of stenting options from the ECASES system and expert experience are provided by investigators, and the stenting option is selected by a dedicated person (nonsurgical participant) according to the subject group. This person then informs the surgical staff, but the source of the option is not revealed, which minimizes confounding factors and bias and results in a reasonable and reliable study design. Additionally, ECASES uses a scale format that can realize specific and quantitative evaluations, and is accurate, fast, and efficient.
